**Discussion:**

This study will prospectively observe elderly patients with SCH who are screened using both age-specific and non-age-specific TSH reference ranges for the elderly population. We will compare the results of elderly patients diagnosed with SCH using different reference ranges and analyze their association with FT_4_ to identify meaningful SCH patients and reduce over diagnosis and over treatment of elderly SCH.

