## Introduction

Subclinical hypothyroidism (SCH) is characterized by elevated serum thyroid-stimulating hormone (TSH) and normal thyroid hormone levels (1). As TSH is considered a good indicator of thyroid function, the diagnosis of SCH is primarily based on TSH levels. However, this can lead to overdiagnosis and overtreatment in elderly patients with SCH, as their TSH levels may naturally increase with age without indicating an underlying thyroid dysfunction (2).

Many studies have found that the incidence rate of SCH increases significantly with age (3, 4), which suggests that we need to consider the impact of aging on the hypothalamic-pituitary-thyroid (HPT) axis. For example, aging may weaken the circadian rhythm of TSH and reduce its responsiveness (5). According to the cross-sectional National Health and Nutrition Examination Survey (NHANES) III, the average TSH of adults aged 80 is 69% higher than that of adults aged 20 (6, 7). Data from Scottish, and Australia also confirm that TSH level increases with age (8–10). Our previous epidemiological survey in ten cities indicated that the prevalence of SCH in people over 65 years old was 19.87% according to the current TSH reference interval, but when the age-specific TSH reference range was used, the prevalence decreased to 3.3% (3). Although the mechanism is unclear, the increase in TSH in the elderly may be a normal phenomenon associated with aging. When the current diagnostic criteria are used, many elderly patients with no clinical significance will be diagnosed.

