### Inclusion criteria and exclusion criteria

Inclusion criteria:

Elderly patients with SCH will be included according to the elderly and the general population-specific reference ranges, respectively.

(1) Inpatients and/or outpatients aged≥60 years.(2) The levels of free triiodothyronine(FT_3_) and FT_4_ are within the normal range.(3) TSH is greater than the upper limit of the normal reference range (old standard) and less than the upper limit of the normal reference range (new standard).

Exclusion criteria:

(1) Does not meet the inclusion criteria, does not sign the consent form, or participates involuntarily.(2) Exit halfway due to various reasons.(3) Unable to cooperate with the project team to complete all inspection contents.(4) Other factors leading to TSH increase. 1) increased TSH caused by measurement errors; 2) convalescence stage of the euthyroid sick syndrome; 3) central hypothyroidism; 4) renal insufficiency; 5) lack of glucocorticoids; 6) the recovery stage of thyroid function in subacute thyroiditis; 7) having taken amiodarone or lithium; 8) other interfering factors.

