### Study follow-up assessments

When a patient has FT_4_ levels below the lower limit of the normal reference range during follow-up, follow-up is terminated and thyroid hormone replacement therapy will be initiated. For patients aged 60 to 70 years, start treatment when TSH≥10mIU/L. For patients aged 71 to 80 years, treatment begins when TSH≥10 mIU/L and is accompanied by symptoms of hypothyroidism. Normal value reference ranges will be established based on the TSH levels of 120 normal elderly individuals over 60. Elderly SCH patients screened according to the TSH reference interval in the normal population and the elderly population will be followed up every 6 months, including the subclinical hypothyroidism questionnaire, the Montreal Cognitive Assessment-Basic (MoCA-B), Hamilton Depression Scale (HAMD), Hypothyroidism Symptom Questionnaire (SRQ), frail scale(FRAIL), fatigue scale, EQ-5D, thyroid function, blood lipid analysis, carotid color ultrasound, and thyroid ultrasound. The estimated sample size is 438. Patients diagnosed with different TSH reference intervals will be compared for cognitive function, depression scores, hypothyroidism, fatigue severity, carotid atherosclerosis, lipid profile, and cardiocerebrovascular complications. Besides, TSH reference intervals will be applied to calculate medical costs and evaluate the economic benefits of multiple follow-ups of patients with SCH. The research design can be seen in **Figure 1**.

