### Data analysis

We will calculate age-specific TSH reference intervals based on the obtained data, analyze the natural outcomes, the occurrence of cardiovascular events, cognitive status, depression, and fatigue of elderly patients with SCH diagnosed under different reference intervals, and conduct economic analysis.

Continuous data will be expressed as mean ± standard deviation or median with a range of quartiles. Classification data will be expressed in numbers with percentages. Cox proportional risk model will be used to evaluate survival results. The variables measured several times during the follow-up period will be compared with the paired t-test according to the clinical management used. The significance level will be set to 0.05, and R software, prodlim, and Cairo software will be used to analyze the data.

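### Grouping patients by which TSH interval diagnoses them makes one comparison group a subset of the other, or leaves it empty under inclusion criterion 3; the comparison needs two disjoint classes fixed on entry TSH

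*Protocol article*

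**What the plan says.** Under Study follow-up assessments, the article states the comparison: "Patients diagnosed with different TSH reference intervals will be compared for cognitive function, depression scores, hypothyroidism, fatigue severity", followed by vascular, lipid and complication outcomes. The Discussion part of the Abstract uses the same grouping: "We will compare the results of elderly patients diagnosed with SCH using different reference ranges". Data analysis also describes outcomes by the interval under which patients were diagnosed.

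On enrolment, the lead sentence of the inclusion criteria reads "Elderly patients with SCH will be included according to the elderly and the general population-specific reference ranges, respectively". Criterion 3 in the same list requires that "TSH is greater than the upper limit of the normal reference range (old standard) and less than the upper limit of the normal reference range", where the second limit is labelled the new standard.

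The Introduction gives the two prevalences from the investigators' own survey: "the prevalence of SCH in people over 65 years old was 19.87% according to the current TSH reference interval", and "when the age-specific TSH reference range was used, the prevalence decreased to 3.3" per cent.

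On size and testing, "The estimated sample size is 438" is given without a derivation or a split by group, and "The significance level will be set to 0.05". Data analysis names a Cox model, with no grouping variable, and a paired t-test for repeated measurements. It names no test between the two diagnostic groups.

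**The concern.** The two diagnoses are not alternatives. One implies the other, because the age-specific cut-off is the higher of the two. The study asks whether patients who lose the label under the age-specific interval differ from those who keep it. That is a contrast between patients whose TSH lies between the two limits and patients above both, and the article never names it.

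The contrast it does name sets everyone above the general limit against the part of that same set above the age-specific limit. The shared patients pull the two averages together, so a real difference looks smaller than it is. In this study a small difference is not a neutral result, because it bears on whether the age-specific interval identifies a distinct group of patients. If criterion 3 governs enrolment instead, there is nobody to place in the second group.

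**Working it through.** **Step 1. Is one group inside the other?** Two places in the article put the limits in the same order. Criterion 3 describes a band above the old limit and below the new one, so the new limit is higher. The Introduction's fall from 19.87% to 3.3% agrees. A TSH above the higher limit is also above the lower one, so the age-specific diagnosis is nested in the general one.

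**Step 2. Who is enrolled?**
- Lead sentence of the inclusion criteria, and Study follow-up assessments: patients identified by either interval are followed. The groups are then nested.
- Criterion 3 as written: only patients between the limits enter. Nobody enrolled is diagnosed by the age-specific interval, so that group is empty.

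These statements cannot all hold, and neither reading gives two separate groups to compare.

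**Step 3. Dilution when the groups are nested.** Let class B be patients above the age-specific limit, class C those between the limits, and A = B + C, with f = n(B)/n(A). Then

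mean(B) − mean(A) = (1 − f) × [mean(B) − mean(C)].

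This is an identity and does not depend on the test.

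**Step 4. Inputs for a size.** The article gives no split, so f is an assumption. The survey ratio gives f = 3.3/19.87 = 0.166. If all 438 patients are above the general limit, 438 × 0.166 ≈ 73 fall in B and 438 − 73 = 365 in C. The total of 438 cannot be reproduced, because no effect size, event rate, power or dropout is stated. It is used here only as a total.

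- Difference retained: 1 − 0.166 = 0.834, or about 83%.
- Standard error assumed by an independent-groups test of 438 against 73, in SD units: √(1/438 + 1/73) = 0.126.
- True standard error of that nested contrast: 0.833 × √(1/365 + 1/73) = 0.107.
- Standard error of the disjoint contrast, 365 against 73: √(1/365 + 1/73) = 0.128.

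**Step 5. Consequence if an ordinary independent-groups test were used.** The test statistic has standard deviation r = √[(1 − f)/(1 + f)] instead of 1. At f = 0.166, r = 0.846. The true two-sided error rate is 2 × P(Z > 1.96/0.846) = 0.020. A simulation of 20,000 trials with 73 and 365 patients gave 0.019.

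| Nested share f | Dilution | True error rate (nominal 0.05) |
|---|---|---|
| 0.10 | 10% | 0.030 |
| 0.166 | 17% | 0.020 |
| 0.30 | 30% | 0.008 |

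Power at the 73/365 split, for assumed differences between B and C:

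| Difference (SD) | Nested, treated as independent | Disjoint |
|---|---|---|
| 0.25 | 36% | 50% |
| 0.35 | 66% | 78% |
| 0.40 | 79% | 88% |

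For 0.35 SD, the nested figure is P(Z > (1.96 × 0.126 − 0.833 × 0.35)/0.107) ≈ 66%. The disjoint figure is P(Z > 1.96 − 0.35/0.128) ≈ 78%. The simulation at 0.40 SD gave 78% and 87%.

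**The case against.** The strongest objection is that the article does not plan the faulty test. A reader might infer that the planned tests treat overlapping patients as independent samples, but the article does not say so. Data analysis names only a Cox model without a group term and a paired t-test. In an ordinary Cox model with one record per patient, a group term gives each patient one value, so double counting would need duplicated records, and nothing suggests that. The choice of test may sit in a full protocol or analysis plan that is not shown. This part of the objection stands: the error-rate and power figures are conditional.

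Second, the wording could be shorthand for disjoint classes, and Figure 1, which is not shown, may define them. That is possible. But every stated form of the comparison groups patients by diagnosing interval, and no sentence says that a patient above both limits counts once.

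Third, criterion 3 as written leaves no overlap at all. That is correct, but it does not rescue the comparison, because it leaves one group empty. Nor would widening criterion 3 alone cure the nesting.

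Fourth, the split is uncertain. The prevalences are for people over 65 while enrolment starts at 60. The new limit may differ from the one behind the 3.3%, since ranges are to be set from 120 normal elderly individuals. The Abstract's restriction to TSH below 10 mU/L could thin the upper class. This stands too, and it is why a range of f is shown.

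Last, the error is conservative and can be repaired from recorded entry TSH, provided both classes are enrolled. That lowers the urgency but does not remove the point.

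**Conclusion.** The point holds as a defect in how the comparison groups are defined, and it should be fixed. Read literally with both kinds of patient enrolled, the groups are nested and the difference in means is understated by the share f, whatever test is used. Read with criterion 3 as written, the comparison cannot be made. That goes beyond detail a journal article may leave out, because the article's own statements produce both outcomes.

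The central size is a 17% dilution, with 10% to 30% for nested shares of 0.10 to 0.30. It rests on carrying the over-65 prevalence ratio into the cohort and on all 438 patients being above the general limit. The true error rate of about 0.020 and the power of 66% instead of 78% at 0.35 SD also require an ordinary independent-groups test, two-sided testing and an assumed effect size. The documents do not support calling this an error in a specified test, and it does not inflate false positives.

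**What to change.** 1. Reconcile criterion 3 with the lead sentence of the inclusion criteria and with Study follow-up assessments, so that they describe one cohort. If the comparison is to stand, the criteria must admit patients of both classes below.
2. In the Abstract's Discussion, Study follow-up assessments and Data analysis, replace the grouping by diagnosing interval with two disjoint classes fixed on entry TSH: (i) above the general upper limit but not above the age-specific one, and (ii) above the age-specific upper limit.
3. Run all between-group comparisons, and any group term in the Cox model, on (i) against (ii).
4. Report the totals diagnosed by each interval as description only, without a test between them.

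The regrouping needs only changed wording and a class variable derived from entry TSH, which is already measured. It adds no patients or examinations to the planned 438. If enrolment has in practice followed criterion 3 as written, class (ii) will be missing, and the report should say that the comparison could not be made.

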**Figure 1 f1:**
[figure not shown]
Study process.

The scoring breakdown of MoCA-B is as follows: visuospatial and executive functioning: 5 points; animal naming: 3 points; attention: 6 points; language: 3 points; abstraction: 2 points; delayed recall (short-term memory): 5 points; orientation: 6 points; education level: 1 point is added to the score if they have 12 years or less of formal education. A total score of 26 or greater is within the normal range. Using HAMD to assess the degree of depression: 10-13 mild; 14-17 mild to moderate; >17 moderate to severe. The FRAIL consists of five questions with a score of 0-5 (0: for the best state, 5: for the worst state), 3-5 for frailty, 1-2 for pre-frailty, and 0 for physical fitness.

### Research quality control

The collection of questionnaire information and the biological specimen will be conducted by doctors, nurses, or investigators with work experience. Data management and quality control will be carried out for data entry, export, storage, and other aspects. Concerning the quality control of biological samples, the collection, pretreatment, transfer, freezing, and other related processes will be carried out in strict accordance with the relevant Standard Operation Procedure standards. At the same time, random inspection will be carried out on all kinds of work from sample collection to detection to ensure sample quality.

The testing and laboratory processing units are the Laboratory of the First Affiliated Hospital of China Medical University and the West China Hospital, Sichuan University. This study will strictly follow the hospital’s laboratory processing approval process for filing and operation.

Concerning data management and security, all kinds of data in this study will be uniformly saved, and all members, temporary employees, and students will sign a confidentiality agreement.

### Data analysis

We will calculate age-specific TSH reference intervals based on the obtained data, analyze the natural outcomes, the occurrence of cardiovascular events, cognitive status, depression, and fatigue of elderly patients with SCH diagnosed under different reference intervals, and conduct economic analysis.

Continuous data will be expressed as mean ± standard deviation or median with a range of quartiles. Classification data will be expressed in numbers with percentages. Cox proportional risk model will be used to evaluate survival results. The variables measured several times during the follow-up period will be compared with the paired t-test according to the clinical management used. The significance level will be set to 0.05, and R software, prodlim, and Cairo software will be used to analyze the data.

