### Study population

We are conducting a prospectively observational study on patients over 60 years of age diagnosed with SCH. The study was conducted in the First Affiliated Hospital of China Medical University and the West China Hospital of Sichuan University. Patients will be included from December 2022 to December 2023, and the follow-up data will be collected until December 2025.

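### The only test named for repeated measures, a paired t-test by clinical management, does not estimate the difference between reference-interval groups that the study sets out to compare

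*Protocol article*

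**What the plan says.** The comparison of interest is given in Study follow-up assessments: "Patients diagnosed with different TSH reference intervals will be compared for cognitive function, depression scores, hypothyroidism, fatigue severity, carotid atherosclerosis, lipid profile". Data analysis repeats it, planning to analyse "cognitive status, depression, and fatigue of elderly patients with SCH diagnosed under different reference intervals".

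For outcomes recorded at more than one visit, Data analysis then fixes one test: "The variables measured several times during the follow-up period will be compared with the paired t-test according to the clinical management used". The only other inferential method named is the Cox model, which is tied to survival results.

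Patients "will be followed up every 6 months", and the calendar is "Patients will be included from December 2022 to December 2023, and the follow-up data will be collected until December 2025". On error control the article says only "The significance level will be set to 0.05".

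Study follow-up assessments also describes when thyroid hormone treatment starts. Depending on age, the triggers are an FT4 below range, a TSH at or above 10 mIU/L, or such a TSH together with symptoms. Follow-up ends when FT4 falls below range.

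**The concern.** The test and the question do not match, in two ways.

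First, a paired t-test on two visits estimates the mean change inside one set of patients. Run separately in two sets, it yields two changes and two p-values, but no estimate of how the sets differ and no interval for that difference. The likely substitute is to report that scores changed significantly in one group and not in the other. That pattern is common even when the true changes are equal, as the working shows.

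Second, the grouping named is clinical management, not reference interval. Treatment during follow-up is decided by TSH, FT4 and symptoms observed after baseline. Groups formed that way reflect how the disease went, so a contrast between them does not answer whether patients labelled by one range fare differently from those labelled by the other.

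A lesser issue is use of the data. Each paired test uses two measurements and omits any patient who lacks one of them, including those whose follow-up stopped because FT4 fell. Those are the patients who progressed.

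**Working it through.** **Measurements per patient.** Enrolment runs from December 2022 to December 2023 and data collection ends in December 2025. Possible follow-up is therefore 24 months (last enrolled) to 36 months (first enrolled). At one visit per 6 months, 24/6 = 4 and 36/6 = 6 follow-up visits; with baseline, 5 to 7 measurements. One paired test uses 2 of them. The last visit that every enrolment date can reach is month 24.

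**Inputs that the article does not give.** The stated sample size is 438, without an effect size, SD, power or group split, so it cannot be reproduced and nothing below depends on how it was derived. The splits and effect sizes here are assumptions:
- Equal split: 438/2 = 219 per group.
- Unequal split: the Introduction reports SCH prevalence over age 65 of 19.87% under the current interval and 3.3% under the age-specific one. If those proportions carried over, 438 × 3.3/19.87 = 72.7, so about 73 patients would have SCH under both ranges and 365 under the current range only.
- True change: identical in both groups, expressed in SDs of the change.

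**Chance that the two groups disagree on significance.** The power of a two-sided paired t-test at 0.05 comes from the noncentral t distribution with n − 1 degrees of freedom and noncentrality d√n. With powers p1 and p2 in independent groups,

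P(discordant) = p1(1 − p2) + p2(1 − p1).

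| Split | True change (SD) | p1 | p2 | P(discordant) |
|---|---|---|---|---|
| 219/219 | 0.10 | 0.314 | 0.314 | 2 × 0.314 × 0.686 = 0.43 |
| 219/219 | 0.20 | 0.838 | 0.838 | 2 × 0.838 × 0.162 = 0.27 |
| 219/219 | 0.30 | 0.993 | 0.993 | 0.01 |
| 365/73 | 0.20 | 0.968 | 0.392 | 0.968 × 0.608 + 0.392 × 0.032 = 0.60 |

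In every row the true between-group difference is zero. At no change at all, discordance is 2 × 0.05 × 0.95 = 0.095. The figure therefore depends heavily on the assumed change and split, and it becomes negligible when both groups are large and the change is big.

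**Number of tests.** Study follow-up assessments lists seven questionnaires: the subclinical hypothyroidism questionnaire, MoCA-B, HAMD, SRQ, FRAIL, fatigue and EQ-5D. If each follow-up visit were tested against baseline (an assumption; the article does not say which visits are paired):
- 7 × 4 = 28 to 7 × 6 = 42 tests per group.
- Expected false positives at 0.05 with no true change: 28 × 0.05 = 1.4 to 42 × 0.05 = 2.1 per group.
- For one questionnaire, the chance of at least one false positive is 1 − 0.95⁴ = 18.5% to 1 − 0.95⁶ = 26.5% if the tests were independent. Simulation with an assumed within-patient correlation of 0.6 and n = 219 gives about 15% to 20%.

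**The case against.** The best defence is that the article never assigns the paired t-test to the between-group question. It may be meant only to describe change over time, with the group comparison left to a fuller plan. That is fair as far as an unnamed test goes, and silence alone would be no finding. But the sentence does fix a method and a grouping for all variables measured several times, and neither serves the comparison stated in the same section. The Cox analysis of endpoint events is untouched by this point.

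Several stronger readings are tempting and are not supported:
- A reader might infer that the plan can use only two visits. That holds for each test; a series of paired tests could cover all visits, but without joint modelling and with more chances of a false positive.
- A reader might infer that treated patients' changes will be distorted by regression to the mean. This is plausible, but it needs measurements after treatment starts. Follow-up ends when FT4 falls, the article does not say whether it continues after a TSH-triggered start, and it does not define the management groups.
- A reader might infer that a t-test is invalid for FRAIL because "The FRAIL consists of five questions with a score of 0-5". The article also gives FRAIL categories and reports categorical data as counts, so a t-test on it is not clearly planned. In large groups, a test of mean change on such a score is usually tolerable.
- A reader might take the 60% as the risk in this trial. It rests on an assumed split; the equal split gives 27% at the same change.

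**Conclusion.** The point stands in limited form: the one test named for repeatedly measured outcomes estimates within-group change, in groups that are shaped by events after baseline, and so cannot deliver the comparison between reference-interval groups. That mismatch follows from the text and needs no numerical assumption.

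The size of the harm does. Reading significance in one group and not the other as a difference would mislead in roughly 27% to 60% of studies for the combinations of 0.10 to 0.20 SD and split highlighted here, and far less often if the change were 0.30 SD in two equal groups. The 1.4 to 2.1 expected false positives per group apply only if every visit is tested against baseline.

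This should be fixed before analysis. It is not graver than that: the study is observational, the endpoint events have their own model, and the remedy is a change of wording.

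**What to change.** First reconcile inclusion criterion 3 with the statement above it, in Inclusion criteria and exclusion criteria, that patients are included by both the elderly and the general-population range. Read literally, criterion 3 admits only TSH values between the old and new upper limits, which would leave no group above the new limit to compare.

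Then replace the paired t-test sentence with, for example:

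> Continuous outcomes measured repeatedly will be analysed with a linear mixed model on all visits, including diagnostic group (reference-interval category by baseline TSH), visit, group × visit and the baseline value, adjusted for age, sex and centre. The result is the group difference at 24 months with its 95% confidence interval. Treatment status during follow-up will be described and will not define the comparison groups.

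The covariance structure, any further covariates and the model for short ordinal scores can be left to the analysis plan.

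The cost is slightly more analysis work and some modelling assumptions. The main one is that visits missing after FT4-triggered termination can be handled given the data already observed; this should be stated and examined. No data beyond those already planned are needed.
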